### Ethical aspects

Patients will be informed orally at the time of admission to the hospital about the nature of the study (including the description of the procedures that will be used, possible discomforts and risks and expected benefits, existing alternative treatment methods, monitoring and assistance approaches, and responsible staff) using accessible language.

Patients will receive clarifications before and during the study regarding the methodology, stating that we will not use a placebo group, and inclusion in a control group is possible. They will be informed about their freedom to refuse to participate or withdraw from the study, at any stage of the research, without any penalty nor prejudice to care; the confidentiality of their data; the absence of reimbursement of expenses resulting from the participation of the research; and the forms of indemnity in the event of any damages resulting from the research in accordance with the ethical standards and regulations of human studies of the Helsinki declaration (2014).

The procedures that we will use do not generate vital risks. The risks are minimal for patients, since we will use low-intensity biphasic electrical currents, which do not generate electrolytic effects on the skin, in addition to surface electrodes. The stimulation will be done only once, thus minimizing the possibility of skin irritation. None of the assessment procedures creates risks for skin injuries. If there are any complications regarding the procedures, patients will be immediately referred to the doctors who accompany them and are part of the project.

The project was submitted to the Research Ethics Committee of the Faculty of Medicine of Bahia, Federal University of Bahia. Patients who agree to participate in the study will sign an informed consent form on admission (extended data), according to Resolution No. 466 of December 12, 2012, of the National Health Council.

The information provided by the patients, as well as all data collected from the research will be kept confidential, to preserve their identity. Data will be kept in a file with a key from the Research Group on Musculoskeletal Dynamics at the Federal University of Bahia (UFBA), under the responsibility of [name] [name].

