### Protocol

This is a randomized, double-blinded, controlled clinical trial that will be carried out in a reference tertiary general hospital in Bahia, Brazil. This protocol has been registered at ReBEC (U1111-1259-1998 on 18
^th^ December 2020) and follows the Standard Protocol Items: Recommendations for Interventional Trials (SPIRIT) checklist (
[name] *et al.*, 2021d). Patients undergoing neurorrhaphy for injuries caused by transection of digital nerves in the hand will be involved in the study. Half the participants will have PES (Endophasys, KLD, Brazil) performed immediately after surgery and before hospital discharge and the other half will receive a SHAM treatment. The participants and outcome assessors will be blinded to patient allocation. The electrodes will be placed in the same position and for the same amount of time for the intervention group as the sham group. The outcome measures evaluators will not know which intervention was assigned to the participants.

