### Intervention

Figure 1 shows a flow diagram of the participants’ journey through the study. Patients will be divided and allocated to two groups: group A (surgery + PES); or group B (surgery + sham). A simple randomization strategy will be performed to achieve balanced groups, using an online resource (
randomization.com). The hidden allocation and electrical stimulation will be performed by a professional not involved in other stages of the study. Opaque and sealed envelopes will be used to address participant allocation. Participants will only be randomized if they provide informed consent to participate in the trial.

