**Figure 1. f1:**
[figure not shown]
Flow chart of the study based on CONSORT criteria.

Following surgery, both groups will additionally receive 1 hour of either electrical stimulation (group A) or sham (group B). In total, two silicone-carbon and gel electrodes (measuring 1 × 1 cm) will be used for all participants, with one placed exactly proximal and the other exactly distal to the surgical site. The two groups will receive the following therapeutic regimens:
•
*Group A: Surgery + PES.* The electrodes will produce a square-pulsed, biphasic, symmetrical current at a frequency of 20 Hz, pulse width of 0.4 ms, and amplitude at the motor threshold of the median nerve, for 1 hour directly after surgery (n = 16);•
*Group B: Surgery + sham PES.* The electrodes will produce a square-pulsed, biphasic, symmetric electric current at a frequency of 20 Hz, pulse width of 0.4 ms, and amplitude at the motor threshold of the median nerve, for 1 hour directly after surgery (the same as Group A) but the electrostimulator will be turned on only until the patient is aware of it, after which the amplitude will be set to zero (n = 16).

In the first post-operative review, the patient will be evaluated by the doctor at the outpatient clinic. A physiotherapist specialized in the area and blinded to the intervention will guide on the rehabilitation protocol that will be monitored remotely by electronic means available to the patient (WhatsApp, Skype, etc.). Patients will undergo a hand sensory re-education protocol based on the one proposed by
Dellon & Jabaley (1982) for a period of 3 months. This protocol involves exercises for discrimination of static and dynamic touch and objects of different shapes, sizes, and textures guided by the physiotherapist, and the patient is also stimulated to perform a home program exercises. This will involve a total of 20 remote monitored sessions lasting about 30 minutes each, carried out, on average, twice per week. No videos or photos of the patients will be acquired to guarantee the patient’s privacy and data confidentiality.

Patients will be evaluated in person after every 10 treatment sessions by the main author of the study, who is responsible for the surgical and postoperative follow-up of the study participants but blinded to group allocation.

Participants must complete a total of 4 face-to-face assessments to document the results:

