### Study status

The study will start after the project has been approved by the Research Ethics Committee (CEP) of the Faculty of Medicine of the Federal University of Bahia, Federal University of Bahia and upon receiving all the materials needed. The study is scheduled to run for 10–12 months from October 2020 to October 2021 as described in
Table 3 (we are at the Treatment Stage according to the Milestone schedule as of February 2020).

**Table 3. T3:** Milestone schedule.

Milestone	Bimonthly periods				
	1	2	3	4	5
Literature review	x	x	x	x	x
Project submission to the ethics committee		x			
Treatment stage (surgical stage, electrostimulation, rehabilitation)			x	x	x
Analysis and writing of clinical results			x	x	x
Analysis and writing of statistical results				x	x
Project qualification			x		
Thesis writing			x	x	x
Submission of articles		x	x	x	x
Thesis defense and submission of the final article				x	x

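### The Ethical aspects section says patients will be told there is no placebo group, but the trial randomises blinded participants 1:1 to sham stimulation

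*Protocol article*

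**What the plan says.** The protocol article, under Ethical aspects, sets out what patients will hear. They are informed orally on admission about the nature of the study, including its procedures, risks and alternatives. They then receive clarifications, before and during the study, about the methodology, "stating that we will not use a placebo group, and inclusion in a control group is possible". The section says that those who agree "will sign an informed consent form on admission (extended data"); the form itself is not reproduced in the article.

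The design is set out elsewhere in the same article:

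- Under Protocol, half the participants receive active peripheral electrical stimulation (PES) and "the other half will receive a SHAM treatment". Electrode placement and session length are matched between the arms. "The participants and outcome assessors will be blinded to patient allocation".
- Under Intervention, group A is surgery plus PES and group B is surgery plus sham, with n = 16 each. In group B, "the electrostimulator will be turned on only until the patient is aware of it, after which the amplitude will be set to zero". Both groups then follow the same sensory re-education programme.
- Under Sample size and patient allocation, the total is 32 patients, 16 per group.

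**The concern.** The two descriptions cannot both be right. A simulated treatment that is matched in set-up and duration, delivers no current once the patient has noticed it, and is given to people who do not know their allocation is a placebo control in all but name. The article nevertheless commits the team to telling patients that there is no placebo group.

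Consent is what is at stake. Whether the stimulation may be simulated is central to a decision to join a sham-controlled trial. A patient told that there is no placebo group could reasonably conclude that any stimulation received will be real throughout. Because the clarifications continue during the study, the statement could also be repeated after enrolment.

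**Working it through.** This is a conflict between statements, so the check is to set them side by side.

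**1. Is group B a placebo control?**

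| Feature | What the article says | Where |
|---|---|---|
| Comparator | Sham stimulation for half the participants | Protocol; Intervention |
| Appearance | Electrodes placed as in the active arm, for the same time | Protocol |
| Active element | Amplitude goes to zero once the patient notices the current | Intervention |
| Knowledge of allocation | Participants blinded | Protocol |

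Taken together, these features make group B a placebo control. The only real current a group B patient receives is the brief initial period, whose purpose is to make the sham convincing.

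**2. Does the article define placebo so as to exclude sham?** No. In describing this trial's own groups it uses the word only in the no-placebo statement, without definition. Group B is called sham everywhere else.

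**3. Does the rest of the sentence repair the statement?** It adds that a patient may be placed in a control group. That tells patients they may not be in the PES arm. It does not say the control involves simulated stimulation, and it follows directly on a denial of placebo.

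**4. How many participants does it concern?** The protocol's own figures are 26 patients before losses and a 20% increase: 26 × 1.20 = 31.2, rounded up to an even 32, or 16 per group. The planned chance of sham is

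16 / 32 = 0.50, that is, 1 in 2.

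Simple randomisation, as named under Intervention, does not by itself guarantee exactly 16 per arm. With equal allocation probability, each person's chance is 1 in 2 whatever the final split.

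**5. Does any analysis figure change?** No. The statement is addressed to patients in general and not to one arm. The sham procedure, sample size and planned tests do not depend on it.

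**The case against.** The best case on the other side has four parts.

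*The section also promises an account of the procedures.* Sham is one of the two procedures, so a team following the whole section might well describe it. This stands, and it limits the finding. A reader might infer that the plan conceals the sham from patients, but the article does not support that. What it gives staff is an inconsistent instruction: describe the procedures, and also say there is no placebo group. The second part is still false and still has to go.

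*The authors may have meant that nobody goes without real treatment.* Both arms receive surgery and rehabilitation, so this is plausible and may explain the wording. The sentence does not say it, and a patient could not be expected to work it out.

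*The consent form is the operative document and is not shown.* This is correct. A reader might infer that enrolled patients were misinformed or that their consent is defective. Nothing in the article establishes either, and the form may describe the sham accurately. The section also provides for oral clarifications, however. If the form is right, the statement described for those clarifications would contradict it.

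*A journal article condenses the full protocol.* That excuses omissions. Here the article makes a positive statement that conflicts with its own design.

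**Conclusion.** The point holds as a false statement in the patient information the article describes: patients are to be told that no placebo group is used, while half of the planned 32 (16, or 50%) are allocated, blinded, to a placebo control. Confidence in the conflict is high because it is read directly from the text. It rests on one judgement, that sham stimulation cut to zero once noticed and given under participant blinding is a placebo control.

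It is not established that sham goes undisclosed, that the consent form is wrong, or that any participant heard the statement. Nor does the article show any bias in the treatment comparison, inflation of the error rate or loss of power. The matter is one of disclosure. It should be corrected because it bears on consent and the correction is simple.

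**What to change.** In the Ethical aspects section, delete the no-placebo clause and replace it with text such as:

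> You have a 1 in 2 chance of receiving sham stimulation, in which the device is switched on briefly and then delivers no current; you will not know which you received. Both groups receive surgery and the same rehabilitation.

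This states the chance of sham without revealing anyone's allocation, so blinding is kept. It also mentions the brief real current at the start of the sham, which a plain description as inactive stimulation would leave out.

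Then check that the participant information sheet and consent form agree. Correct them, and re-inform participants, only if the no-placebo statement was actually used.

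The cost is a wording correction, with an ethics amendment if the approved text carries the same statement. The sham procedure, sample size and analysis stay as they are.

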### Plans for dissemination

The study findings will be published in a thesis and research article. This work is linked to the master’s degree of [name] (Graduate Program of the Bahiana School of Medicine and Public Health, under the guidance of [name] [name] and co-supervision of [name]).

### Study status

The study will start after the project has been approved by the Research Ethics Committee (CEP) of the Faculty of Medicine of the Federal University of Bahia, Federal University of Bahia and upon receiving all the materials needed. The study is scheduled to run for 10–12 months from October 2020 to October 2021 as described in
Table 3 (we are at the Treatment Stage according to the Milestone schedule as of February 2020).

**Table 3. T3:** Milestone schedule.

Milestone	Bimonthly periods				
	1	2	3	4	5
Literature review	x	x	x	x	x
Project submission to the ethics committee		x			
Treatment stage (surgical stage, electrostimulation, rehabilitation)			x	x	x
Analysis and writing of clinical results			x	x	x
Analysis and writing of statistical results				x	x
Project qualification			x		
Thesis writing			x	x	x
Submission of articles		x	x	x	x
Thesis defense and submission of the final article				x	x

## Discussion

The main contributions of this study are discussed below.

### Scientific impact

The use of electric currents to promote peripheral nerve regeneration has been studied in experimental animal models, and, essentially, through invasive techniques. Surface electrodes are cheaper and offer minimal potential risk for the patient. Despite these advantages, in general, studies with humans address the use of electrical currents to generate contraction of the denervated muscle, but not to directly promote regeneration. This study could provide novel, useful, and practical strategies to treat patients with peripheral nerve damage.

### Technological impact

We are involved with a project that has already been approved by the PAPPE Public Notice of the State of Bahia Foundation for Research Support, for the creation of functional electrical stimulation devices for patients with peripheral nerve damage. For this collaboration between the Polytechnic School and the Institute of Health Sciences, both from UFBA, some data would be important for the manufacture of these devices. It is necessary to know whether electrical currents, as they are being tested in this project, may or may not influence peripheral nerve regeneration, so that we can complete the planning of the functional electrical stimulation device.

### Economic and social impact

Peripheral nerve injuries are clinical entities that are usually underdiagnosed and undertreated. This has consequences, such as worker incapacity, with repercussions on their families and means of work. Transection injury treatments are usually exclusively surgical. However, strategies to speed recovery and return to function are extremely important both for the patients to have a greater chance of returning to work and to minimize costs related to associated complications.

In the city of Salvador, patients with peripheral nerve damage who have low purchasing power are usually operated on at the general hospital of the state and tend to have difficulties in carrying out their rehabilitation, as they do not have a service available for this situation. This research project is part of a larger perspective, with the creation of a reference service for the rehabilitation of patients with peripheral nerve damage, which should work within the Physiotherapy Service of [name] University Hospital Complex, Federal University of Bahia. In addition to patients with digital nerve injuries, this service can serve all other patients who are operated on in acute situations or who have chronic neuropathies and need specialized care.

## Data availability

### Underlying data

No data are associated with this article.

### Extended data

Figshare:

List of study materials:
https://doi.org/10.6084/m9.figshare.13636685 (
[name] *et al.*, 2021a)

Available facilities:
https://doi.org/10.6084/m9.figshare.13636694 (
[name] *et al.*, 2021b)

Participant information sheet and consent form:
https://doi.org/10.6084/m9.figshare.13681825 (
[name] *et al.*, 2021c)

### Reporting guidelines

Figshare: SPIRIT checklist for ‘Influence of surface peripheral electrical stimulation on nerve regeneration after digital nerve neurorrhaphy: study protocol for a randomized clinical trial.

https://doi.org/10.6084/m9.figshare.13584764.v1 (
[name] *et al.*, 2021d)

Data are available under the terms of the
Creative Commons Zero “No rights reserved” data waiver (CC0 1.0 Public domain dedication).
